##### Secondary analysis

The continuous secondary outcomes and baseline characteristics, measured at the different time points, will be used in a linear mixed model allowing correction for repeated measurements from the same patient to compare their profiles over time and identify at which time points the groups differ. Other variables such as age, gender and tinnitus grade can also be included in these models.

Considering this is a non-inferiority trial, primary and secondary endpoints are analysed in first instance in the per-protocol population. The per-protocol population are all eligible patients who adhered to the complete protocol. The intention-to-treat population will be taken into consideration in a sensitivity analysis afterwards.

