##### Health outcomes

To evaluate the potential health gains of ST patients due to the blended physiotherapy program, this study will employ quality-adjusted life years (QALYs). QALYs combine both length of life (LoL) and health-related quality of life (HRQOL) in one composite measure. One QALY gained because of the blended physiotherapy program can thus be interpreted as living one additional year in perfect health due to the proposed treatment.

HRQOL will be determined using the EuroQoL EQ-5D-5L questionnaire, which is discussed elaborately above. While we expect HRQOL to be equal across groups at visit 1, data collection at baseline is necessary to be able to adjust for possible, but unlikely, baseline differences between the control group and intervention group. The resulting health states will be converted into health utilities (ranging from 0 to 1 with 0 equal to death and 1 to perfect health) using the recently published utility value sets for Belgium and will at its turn be used to calculate QALYs [61]. Next, incremental health gains will be calculated by comparing the QALYs of the intervention group to the control group.

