## Discussion

The aim of this study is twofold, namely investigating the effectiveness and cost-effectiveness of a blended physiotherapy program for ST, including a smartphone application designed to increase therapy compliance and provide tinnitus counselling.

The study population in scope are adult ST patients. Patients will be diagnosed with ST by a multidisciplinary team of specialists in their field. This team will exist of ENT doctors, audiologists, physiotherapists and psychiatrists. The ENT doctors and audiologists will examine the presence of possible hearing loss, underlying disorders and tinnitus. The physiotherapists will assess the presence of neck and jaw dysfunctions and the link between these dysfunctions and the tinnitus using the diagnostic criteria for somatic tinnitus [31]. Any active psychiatric disorders, such as anxiety or depression disorders, will be excluded by the psychiatrist. This extensive diagnostic process by a multidisciplinary team is a major strength of our study.

The main scientific risks associated with the present study protocol are insufficient enrolment and patient drop-out. However, every year 2500 patients suffering from tinnitus seek help at the ENT department at UZA. As a quarter of these patients are diagnosed with ST, a maximum of 625 patients will be available for inclusion in our study on an annual basis. Therefore, we expect sufficient enrolment during the inclusion period of 2.5 years. In addition, the willingness of participants to complete the full treatment program and all follow-up tests is crucial for the power of the study results. The risk for drop-out is especially high in patients who do not experience the expected treatment results. To maximise treatment adherence and minimise drop-out, patients will be encouraged to complete the treatment and follow-up phase by the therapist, the study nurse and the researcher. Nonetheless, a drop-out of 10% was considered in the sample size calculation.

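### The non-inferiority rationale for leading with the per-protocol set is extended to secondary endpoints that have no margin and are analysed for differences

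*Protocol article*

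**What the plan says.** The rule on analysis sets is in the protocol article under *Data analysis and statistics*, *Effectiveness analysis*, *Secondary analysis*. It gives the non-inferiority design as its reason and says that "primary and secondary endpoints are analysed in first instance in the per-protocol population". The set is then defined: "The per-protocol population are all eligible patients who adhered to the complete protocol". The alternative comes second: "The intention-to-treat population will be taken into consideration in a sensitivity analysis afterwards".

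The paragraph above that rule describes linear mixed models for the continuous secondary outcomes. One of their stated purposes is to "identify at which time points the groups differ".

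The margin of 6.5 points and the non-inferiority hypothesis appear only for TFI change from baseline to 1 month (*Sample size and power*; *Primary analysis*). No secondary outcome has a margin.

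The *Discussion* says of drop-out: "The risk for drop-out is especially high in patients who do not experience the expected treatment results".

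On the economic side, EQ-5D-5L, iPCQ and the diary of medical costs are subsections of *Secondary outcome measures*. The *Cost-effectiveness analysis (CEA)* section stands beside the *Effectiveness analysis* section and names no analysis set. Under *Health outcomes* it says only that "incremental health gains will be calculated by comparing the QALYs of the intervention group to the control group".

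**The concern.** The usual case for giving the per-protocol set weight in a non-inferiority trial is that poor adherence can pull the arms together in an intention-to-treat analysis and so make a worse treatment look acceptable. That argument needs a margin and a claim of similarity. It gives no reason to lead with the per-protocol set when the aim is to find differences. There, selecting on adherence after randomisation gives up the protection of randomisation and gains nothing in return.

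The selection is also unlikely to be neutral. By the article's own account, patients without benefit are the likelier ones to leave. What adherence demands also differs by arm. The experimental arm has six sessions, a daily app exercise programme and two app counselling sessions a week. The control arm has twelve sessions and encouragement to exercise at home. The app is meant to improve compliance, so selecting on adherence conditions on part of what the programme is designed to change.

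At stake is the credibility of the leading results for neck and jaw function, audiology, loudness, mood and hyperacusis. If the rule is read literally, EQ-5D-5L and iPCQ are also affected. Which set decides the primary TFI claim is a separate question and is not raised here.

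**Working it through.** **1. The plan's own figure.** Inputs from *Sample size and power*: margin 6.5, SD 20, one-sided alpha 0.025, power 80%, true difference 0.

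- Normal approximation: n = 2 × SD² × (z₀.₉₇₅ + z₀.₈₀)² / margin² = 2 × 400 × (1.960 + 0.842)² / 42.25 = 148.6, so 149 per group.
- Noncentral t: power is 79.8% at 149 and 80.1% at 150 per group. The stated 150 reproduces.
- Drop-out: 150 / 0.90 = 166.7, so 167 per group and 334 in total. This also reproduces.

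The calculation concerns the primary comparison only. Changing the lead set for secondary endpoints leaves it untouched.

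**2. How many patients the rule removes from the leading secondary analyses.** Number removed = 334 × exclusion rate, taken as equal in both arms.

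| Exclusion rate | Removed | Basis |
|---|---|---|
| 5% | 16.7, about 17 | assumed |
| 10% | 33.4, about 33 | equals the planned drop-out |
| 20% | 66.8, about 67 | assumed |
| 30% | 100.2, about 100 | assumed |

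The 10% is a drop-out allowance. Patients who stay in the trial but do not adhere would add to it. The *Background* reports that two thirds of patients do not keep up daily home exercises. That is not a forecast for this trial, but it shows that rates above 10% are possible if exercise adherence counts towards the per-protocol definition.

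**3. What selection does to a difference.** In one arm, let a fraction f be excluded, and let g be the mean outcome of those kept minus the mean of those excluded. The all-randomised mean is then the per-protocol mean minus f × g. The per-protocol difference between arms therefore departs from the all-randomised difference by f(E) × g(E) − f(C) × g(C), where E is experimental and C is control. This is zero only if the two products are equal. The document gives no values for g and no reason to expect equality, so neither size nor direction can be calculated.

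**4. Does the rationale reach the secondary endpoints?**

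| | Margin | Aim | Lead set stated |
|---|---|---|---|
| TFI change at 1 month | 6.5 | non-inferiority | per-protocol |
| Secondary mixed models | none | find differences | per-protocol |
| Cost-effectiveness | none | incremental cost per QALY | none named |

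The reason given belongs to the first row. The rule is applied to the second. Whether it reaches the third depends on which part of the article is followed. The outcome list places EQ-5D-5L and iPCQ among the secondary outcomes, while the analysis section treats the economic evaluation separately.

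**The case against.** The strongest reply is that intention-to-treat results are already planned, directly after a sentence that covers secondary endpoints. Nobody is discarded, and the dispute is only about which result leads. That is fair and limits the severity. It does not remove the point, because the leading analysis is the one on which conclusions will rest, and the reason given for the choice does not apply.

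A reader might infer more on the economic side, namely that the lead incremental cost-effectiveness ratio (ICER) will be per-protocol. The document does not show this. The rule sits under the effectiveness heading, the parallel economic section states no restriction, and base-case direct costs come from hospital financial records, which are not listed as a secondary outcome. In a condensed article, an unstated economic population alone would be no finding. What stands is narrower: the wording, read with the outcome list, covers EQ-5D-5L and iPCQ, and its reach should be settled.

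A reader might also infer that analysing completers fixes the cost result, since they would differ by exactly six sessions. Sessions are only one input. Consultations, scans, medication, outside care, lost productivity and QALYs all still vary. If a fraction x of each arm stopped halfway, the saving would be 6 × (1 − x/2), or 5.7 sessions at 10%. That rests on an assumed stopping pattern, counts sessions rather than euros or QALYs, and does not measure bias in the ICER.

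Finally, changing the set does not by itself supply missing data. During treatment the iPCQ is completed at treatment sessions, and the diary is described for the period between the two follow-up visits. Outside costs of early stoppers may go unrecorded whichever set is used. This stands as a limit on what the change can achieve.

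**Conclusion.** The point holds for the secondary difference analyses and should be corrected. The article applies a non-inferiority argument to endpoints with no margin, and the selection that results is, by its own account of drop-out, probably related to outcome. About 33 of 334 patients leave the leading secondary analyses if exclusions equal the planned 10%. Larger numbers rest on assumed rates.

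For EQ-5D-5L and iPCQ the point is one of scope: the literal wording includes them, and the economic section neither adopts nor excludes the rule. The document contains no cost or utility figures, so bias in the ICER cannot be computed. The primary analysis and the sample size are unaffected.

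**What to change.** 1. Under *Secondary analysis*, limit the per-protocol sentence to the primary TFI non-inferiority comparison.
2. In the same place, make all randomised patients, as allocated, the lead set for the secondary difference analyses, with the per-protocol set as a sensitivity analysis.
3. Under *Cost-effectiveness analysis (CEA)*, state that the per-protocol rule does not carry over, and that the lead analysis uses all randomised patients as allocated and costs the sessions actually attended.

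The cost is mainly wording, since the intention-to-treat analysis is already planned. The 150, 167 and 334 stay as they are. Some handling of missing data is needed. The planned mixed models can use every observed visit if data are missing at random, but the expected link between poor response and drop-out calls for a check on that assumption. Missing cost and utility data need a stated approach. Intervals may be somewhat wider.

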Among the many potential influencing factors of tinnitus, one group exists where the tinnitus is influenced by alterations in somatosensory afference from the cervical spine or temporomandibular area, caused by, for instance, increased muscle tension or movement restrictions. This type of tinnitus is called somatic or somatosensory tinnitus (ST) and is estimated to be present in approximately 25% of tinnitus patients [11–13]. Previous studies showed that a multimodal physiotherapy treatment directed to cervical spine and temporomandibular joint (TMJ) dysfunctions can provide tinnitus relief in ST patients [14–22]. The multimodal physiotherapy treatment comprises a combination of (home) exercises, manual mobilizations and techniques to decrease muscle tension tailored to the patient’s specific cervical spine and/or TMJ dysfunction [14–17].

While the effectiveness of this multimodal physiotherapy program has been proven, there are still opportunities for improvement. Firstly, the efficacy of the home exercises could be increased, as two thirds of patients are not compliant in performing daily home exercises, and others experience difficulties to perform the exercises correctly without the guidance of a physiotherapist [23]. Secondly, the associated symptoms and comorbidities of tinnitus often demand a more multidisciplinary approach [4–7]. Apart from the physiotherapy program, patients would also benefit from additional psychological counselling and advice to account for the mental burden that comes with tinnitus [12]. Due to a lack of knowledge about tinnitus, physiotherapists often do not provide the additional tinnitus counselling, or patients receive inaccurate advice that may counteract the positive effects of the multimodal treatment. This results in suboptimal care for ST patients and often recurrent complaints that require regular treatment series in the long term. As such, ST patients would benefit from additional support to increase exercise compliance on the one hand and from the addition of psychological counselling on the other hand [4–7, 12, 23].

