#### Blended physiotherapy program (experimental treatment)

The experimental group will receive a blended physiotherapy program consisting of only six instead of twelve physiotherapy treatments over a period of 12 weeks, meaning one treatment session of 30 min every 2 weeks. In addition, a smartphone application will offer the patients a daily exercise program, based upon the standard physiotherapy treatment for ST [14–22], and psychological tinnitus counselling. This tinnitus counselling program consists of two sessions a week and is developed by psychologists of the University of Regensburg [64, 65]. Before the start of the program, the exercises will be tailored to the area, type and degree of the patient’s dysfunctions. During the six physiotherapy treatment sessions, patients will, if needed, receive manual mobilisations to increase mobility of the neck and/or temporomandibular joints or manual techniques to decrease muscle tension in neck and jaw muscles [14–22]. Additional counselling on knowledge about neck and jaw pain and advice about posture and movement habits will also be provided by the physiotherapist during these six treatment sessions.

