### Sample size and power

The study is designed as a non-inferiority trial of a continuous response variable comparing independent control and experimental subjects. The primary outcome is the change in TFI from baseline to 1-month follow-up. We hypothesise that there is no significant difference between the control and experimental group for this outcome. A non-inferiority margin is chosen at 6.5 points, being half of the minimally clinically important difference [66]. Assuming a standard deviation of 20 points (SD found in international literature [67] as well as in previous performed own studies [14, 18]) and a significance level (*α*) of 0.025, an achieved sample size of 150 patients per group is required to have 80% power to show non-inferiority using a one-sided, independent samples *t*-test. Considering a possible 10% drop-out, based on previous studies in ST [14, 37], 167 patients will be recruited into each group. Hence, a total of 334 patients will be recruited for the study.

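### The non-inferiority decision rests first on the per-protocol set, with intention-to-treat only a later sensitivity analysis and no rule for disagreement, so it is open to selection bias of unknown direction

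*Protocol article*

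**What the plan says.** The rule stands in the protocol article under Data analysis and statistics, Secondary analysis, but it covers the primary endpoint too: "primary and secondary endpoints are analysed in first instance in the per-protocol population". The reason given is that this is a non-inferiority trial. The set is defined as follows: "The per-protocol population are all eligible patients who adhered to the complete protocol". Of the alternative, the article says: "The intention-to-treat population will be taken into consideration in a sensitivity analysis afterwards". It does not say what is concluded if the two sets disagree.

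Under Primary analysis, the decision compares a two-sided 95% confidence interval for the difference in TFI change with a margin of 6.5 points.

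Three other places bear on who ends up in the per-protocol set:
- The Discussion says: "The risk for drop-out is especially high in patients who do not experience the expected treatment results". It names no arm.
- Sample size and power allows for 10% drop-out and does not split it by arm.
- The two intervention sections ask different things of patients. Controls attend twelve weekly sessions. The experimental arm attends "only six instead of twelve physiotherapy treatments over a period of 12 weeks", with daily app exercises and two counselling sessions a week in the app.

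**The concern.** A per-protocol set is chosen by what happens after randomisation. Here the authors themselves expect one route out of it, drop-out, to depend on outcome. The other route, non-adherence, is likely to work differently in the two arms, because the tasks differ and the app is designed to change compliance. The Background reports that "two thirds of patients are not compliant in performing daily home exercises" under existing care. The patients compared are then no longer the groups that randomisation made alike.

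The primary conclusion is at stake. If the arm that does worse loses more of its poor responders, the arms look closer than they are, and non-inferiority is claimed too often. If the control arm loses more, a treatment that is truly non-inferior can fail. Without a rule for disagreement, the reading of a split result would be settled after the data are seen.

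The stated reason also does not reach the secondary endpoints. Their mixed models are meant to "identify at which time points the groups differ". That is a test for difference, and the argument that intention-to-treat may blur differences and so favour non-inferiority does not apply to it.

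**Working it through.** **The plan's own figure.** Inputs from Sample size and power: margin 6.5, SD 20, one-sided α 0.025, power 80%, true difference 0.
- n per arm = 2 × (1.960 + 0.842)² × 20² / 6.5² ≈ 149. The exact t-test gives power 0.798 at 149 and 0.801 at 150, so the stated 150 is right.
- 150 / 0.9 = 166.7, rounded up to 167 per arm, 334 in total. This is also right.

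**False-claim rate under selection.** Differences are written as experimental minus control TFI change, so positive means worse for the experimental arm. The true difference is set at the margin, 6.5, where the error should be 2.5%. Each arm starts with 167 patients and SD 20. Assumption, not in the documents: the log-odds of exclusion rise linearly with the patient's own outcome, by the same rule in both arms. D is the mean difference among patients kept, and SE is its standard error from the variances and numbers kept.

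False-claim rate = Φ((6.5 − D)/SE − 1.96)

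With 10% excluded overall:

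| Odds ratio per SD of worse outcome (assumed) | D | SE | False-claim rate |
|---|---|---|---|
| 1.0 | 6.50 | 2.31 | 2.5% |
| 1.5 | 6.41 | 2.29 | 2.7% |
| 2.0 | 6.25 | 2.26 | 3.2% |
| 2.7 | 6.05 | 2.23 | 3.9% |
| 4.5 | 5.72 | 2.17 | 5.5% |

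Example at 2.7: (6.5 − 6.05)/2.23 − 1.96 = −1.76, and Φ(−1.76) = 3.9%. The mechanism is that the worse arm has more poor responders to lose: at 2.7 the one rule excludes about 8.7% of controls and 11.3% of experimental patients. If the set excludes 20% (assumed), the rates at 2.7 and 4.5 are about 5% and 8%. At 33% (assumed) they are about 6% and between 9% and 10%.

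**The same model with an arm-specific shift.** Odds ratio 2.7, about 10% excluded overall:

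| Excluded, control v experimental | D | False-claim rate |
|---|---|---|
| 6.7% v 13.3% | 5.4 | 7.2% |
| 8.7% v 11.3% (one rule for both) | 6.05 | 3.9% |
| 10.3% v 9.7% | 6.6 | 2.2% |
| 11.5% v 8.5% | 7.0 | 1.4% |

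The inflation has gone once the two arms lose about equal shares.

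**A second model.** A fixed share of non-responders is excluded; control mean improvement is assumed to be 13 points and non-response an improvement below 13.
- Excluding 20% of non-responders in both arms gives no bias and 2.5%.
- Excluding 20% in the experimental arm and 10% in the control arm gives 5.7%; 30% v 10% gives 13%; 40% v 10% gives 27%.
- Excluding 10% in the experimental arm and 20% in the control arm gives 0.9%; 10% v 30% gives 0.2%.
- The zero bias under equal exclusion depends on placing the cut-off at the control mean. With a cut-off of 0 and 40% of non-responders excluded in both arms, D is 5.84 and the rate is 4.8%.

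**The case against.** Leading with the per-protocol set is a familiar convention in non-inferiority trials, and the article gives that as its reason. Intention-to-treat is prespecified, so both results will be available. This stands as far as it goes. But the convention rests on the worry that intention-to-treat alone may blur a difference, which is an argument for requiring both sets and not for ranking one below the other.

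A reader might go further and infer that the lead analysis is biased towards non-inferiority. The documents do not support that. The Discussion names no arm, the 10% allowance is not split, and no strength of selection is given. The app is meant to raise compliance, and controls must attend twice as many sessions, so heavier exclusion in the control arm is at least as plausible; that turns the bias the other way.

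A reader might also infer that the plan lets a per-protocol claim stand against a contrary intention-to-treat result. The text does not say so. It says that per-protocol comes first and that intention-to-treat is considered afterwards. The defect is the missing rule, not a stated permission.

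Finally, the handling of missing 1-month scores and penalised sensitivity analyses may be in an analysis plan that is not shown, so their absence from the article is not counted here.

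**Conclusion.** The point holds in this form: the primary decision is taken first in a set selected after randomisation, by a process that the protocol itself expects to depend on outcome, and nothing says what follows if intention-to-treat disagrees. The comparison is open to selection bias.

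Under one exclusion rule for both arms, the models give a lean towards non-inferiority in nearly every setting tried. At the planned 10% it is modest, from 2.7% to 5.5% against 2.5% nominal. Differences between the arms matter more, and they can raise or lower the error. All of these sizes rest on assumed selection strengths and exclusion rates; only the margin, SD, group size and 10% allowance come from the protocol. Confidence is high on the structural weakness and low on its direction.

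For the secondary endpoints the matter is simpler: the reason given for per-protocol first does not apply to tests for difference. This does not affect the primary claim.

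**What to change.** Before unblinding, replace the rule with two sentences to this effect:
- Non-inferiority is declared only if the upper limit of the two-sided 95% confidence interval for the difference in TFI change (experimental minus control) is below 6.5 in both the intention-to-treat set (all randomised patients, as allocated) and the per-protocol set.
- Secondary endpoints are analysed first by intention-to-treat, with per-protocol as the supporting analysis.

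The first sentence also supplies the missing rule: if the sets disagree, non-inferiority is not declared.

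The cost is wording and little extra analysis, since both analyses are already planned. The sample-size formula is unchanged. With a true difference of 0 and SD 20, power in a single set is 80.4% at 150 per arm and 84.4% at 167 (normal approximation). Joint power cannot exceed the lower of the two sets' values and will be somewhat below it, so the claim becomes slightly harder to reach. The sets overlap heavily, which should keep that loss small.
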